#### Sample size calculation

The study will investigate whether a significant difference can be observed between the prevalence of PPD in fathers within the first year after childbirth and the prevalence of depressive symptoms in a matched sample of men without recent paternity. The a priori calculation of statistical power is based on a point prevalence of 5.3% in the control group (95% confidence interval 4.3–6.3%), which corresponds to the incidence of depressive symptoms in men according to the PHQ-9 standard data [48]. Compared to reported prevalence rates, an increase of more than 50% in the point prevalence in fathers of an infant would be relevant. This corresponds to a point prevalence of at least 8.0%. According to the meta-analysis by Cameron et al. (2016), the point prevalence of PPD in fathers in the first year after childbirth lies between 7.2 and 9.6% [9]. Therefore, a potential prevalence of 8.0% is not only a realistic outcome considering the results of previous studies, but would also represent a relevant increase in the rate of depressive symptoms. To be able to detect the difference between the population prevalence of 8.0% in fathers of an infant and 5.0% in the control group with a significance level of 0.05 and a power of 80% in a Chi-square test, data from a total sample size of 2300 participants are necessary.

In Freiburg and Mannheim together, about 5500 children are born each year [61, 62]. Out of these, 4600 fathers of an infant will be randomly selected, meaning 2300 fathers of an infant per city. In addition, a control group (*n* = 4600; 2300 per city) matched according to age, nationality, and marital status will be generated. Thus, a total of 9200 potential participants will be contacted. Based on response rates from other anonymized postal surveys, a dropout rate of about 75% is expected for this study. Already included in these dropout calculations are those men who cannot participate due to incorrect address information. However, the obtained sample size will be sufficiently large to reveal small differences in the prevalence of depressive symptoms among the fathers of an infant (ω = 0.1) for each month after birth with a power > 80% using the Chi-square test.

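### The sample size uses a control prevalence of 5.0%, although the calculation is said to rest on 5.3%; at 5.3%, 2300 respondents give about 74% power (two-sided), not 80%

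*Protocol article*

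**What the plan says.** All of this stands in one paragraph of the protocol article, Statistical methods, Sample size calculation.

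- Basis for the control group: "The a priori calculation of statistical power is based on a point prevalence of 5.3% in the control group", with a 95% confidence interval of 4.3% to 6.3%, taken from PHQ-9 standard data.
- Relevant effect: "an increase of more than 50% in the point prevalence in fathers of an infant would be relevant". The next sentence puts a figure on it: "This corresponds to a point prevalence of at least 8.0" per cent.
- Contrast used for the sample size: "8.0% in fathers of an infant and 5.0% in the control group with a significance level of 0.05 and a power of 80" per cent. The test is the chi-square test, and the total comes to 2300.
- Expected yield: 9200 men contacted, half of them fathers, with about 75% not responding.

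Under Analyses, the article adds that the matching cannot be used in the evaluation, so the comparison is between independent samples.

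**The concern.** The paragraph uses two different control prevalences for one calculation. The 8.0% can only have been derived from 5.3%, since 1.5 × 5.3% = 7.95%; half as much again on 5.0% would be 7.5%. The sample size sentence keeps the 8.0% but sets it against 5.0%. The effect used for sizing is therefore larger than the effect declared relevant.

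This is the only power statement for the primary comparison, and the design has no slack to absorb the difference. The expected yield is 9200 × 0.25 = 2300, exactly the number called necessary, and the analysis cannot regain precision from the matching. If power at the smallest relevant effect is nearer 74% than 80%, the type II error there is about 26% instead of 20%. A non-significant result would then be read as stronger evidence against a relevant increase than the design supports.

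**Working it through.** **Inputs.** From Sample size calculation: control rate p1 = 5.3% (declared basis) or 5.0% (sample size sentence); rate in fathers p2 = 8.0%; alpha 0.05; power 80%; total 2300. Two assumptions are mine. The test is taken as two-sided, because the article does not state sidedness. The groups are taken as 1150 each, because equal numbers are contacted and equal response is assumed.

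**Formulas.** Let d = p2 − p1, p̄ = (p1 + p2)/2, s0 = √[2p̄(1 − p̄)] and s1 = √[p1(1 − p1) + p2(1 − p2)].

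- Size per group: n = [(1.960·s0 + 0.842·s1)/d]²
- With continuity correction: n_c = (n/4)·[1 + √(1 + 4/(n·d))]²
- Power at n per group: Φ[(d·√n − 1.960·s0)/s1], with d replaced by d − 1/n for the corrected test

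**Step 1: reproduce the plan's figure (5.0% versus 8.0%).** d = 0.030, s0 = 0.3486, s1 = 0.3480.

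- n = [(1.960 × 0.3486 + 0.842 × 0.3480)/0.030]² ≈ 1059 per group, 2118 in total.
- Corrected: 1125 per group, 2250 in total.
- Power at 1150 per group: Φ[(0.030 × 33.91 − 1.960 × 0.3486)/0.3480] = Φ(0.960) = 83.1%; corrected, 80.9%.

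So 2300 is consistent with 5.0%, most closely with the continuity-corrected calculation rounded up.

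**Step 2: the declared basis (5.3% versus 8.0%).** d = 0.027, s0 = 0.3524, s1 = 0.3518.

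- Power at 1150 per group: Φ[(0.027 × 33.91 − 1.960 × 0.3524)/0.3518] = Φ(0.640) = 73.9%; corrected, 71.1%. Exact binomial enumeration gives 74.2% and 71.4%.
- Size for 80% power: 1336 per group, 2672 in total; corrected, 1409 and 2818. These are 16% and 23% above 2300 (2672/2300 = 1.16; 2818/2300 = 1.23).
- Rate in fathers at which 2300 gives 80% power against 5.3%: 8.23% (uncorrected).
- An increase of exactly one half (5.3% versus 7.95%): power 72.4%.

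**Step 3: relative effects.** 8.0/5.3 = 1.51; 8.0/5.0 = 1.60.

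**Step 4: sensitivity to the control rate, within the quoted interval of 4.3% to 6.3%** (two-sided, uncorrected, 1150 per group).

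| Control | Fathers fixed at 8.0% | Fathers at 1.5 × control |
|---|---|---|
| 4.3% | 95.9% | 62.8% (6.45%) |
| 5.3% | 73.9% | 72.4% (7.95%) |
| 6.3% | 35.3% | 80.1% (9.45%) |

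The two columns answer different questions. With fathers fixed at 8.0%, the relative increase falls from 86% to 27% as the control rate rises. Only the last column holds the relative effect constant.

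**The case against.** The strongest counter-argument concerns sidedness. The Objectives section states a directional hypothesis, and the sample size section does not say whether the test is one- or two-sided. With one-sided alpha 0.05, 5.3% versus 8.0% needs 2104 respondents (2250 corrected), and 2300 gives 83.0% power. The corrected total equals the two-sided total for 5.0% versus 8.0%. The figure 2300 alone therefore cannot show which control rate was used, and 5.0 could be a misprint for 5.3 in a one-sided calculation. This stands as far as it goes: the 74% is conditional on a two-sided test. It does not rescue the text. The section asks "whether a significant difference can be observed between the prevalence of PPD in fathers" using a chi-square test, no one-sided test is stated anywhere, and the sample size sentence prints 5.0%. If a one-sided calculation was meant, then 5.0% is wrong and the sidedness must be given; the sentence needs correcting on either reading.

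Other points:

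- The relevance criterion is a floor, and 5.0% lies inside the quoted interval, so 5.0% versus 8.0% is not excluded by it. True, but the interval would equally admit 6.0%, and it gives no reason to replace the declared basis with a more favourable value.
- At the pooled prevalence of 8.4% cited in the Background, two-sided power against 5.3% is 83.8%. Also true; the shortfall is at the smallest relevant effect. But that is the effect the section chose for sizing, and at 7.2%, the lower limit it quotes for fathers, power is only 46.9%.
- Power running from 96% to 35% over the control interval is not power for a constant relative effect. This is right, and the last column of the table gives that version.
- Data collection had ended by March 2019, so the sample cannot change. Correct. What remains to be corrected is the claim made for the design, and analysis was still under way in August 2019.

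**Conclusion.** The concern holds. The declared control prevalence and the one used for the sample size contradict each other within one paragraph, and the substitution favours the design. For the smallest effect the plan calls relevant, 5.3% versus 8.0%, 2300 respondents give about 74% power (71% with continuity correction) instead of 80%; reaching 80% would need 2672 to 2818. This rests on a two-sided test at 0.05 and 1150 respondents in each group. Unequal response would lower power further; a one-sided test would give 83%, but the article does not provide for one. The contradiction between 5.3% and 5.0% depends on none of these assumptions.

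**What to change.** Restate the calculation on the declared 5.3% and state the sidedness. Suggested wording: *With 2300 respondents (1150 per group), the two-sided chi-square test at the 0.05 level has about 74% power to detect 5.3% versus 8.0%, and 80% power to detect 5.3% versus about 8.2%.*

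Add power over control rates from 4.3% to 6.3%, saying whether the rate in fathers is held at 8.0% or moves with the control rate. Delete the 5.0%, or give the reason for using it and explain how the effect declared relevant follows from it.

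The cost is a change of wording in one section and a less favourable power statement. No further recruitment is required, and the primary test and the data stay as they are.

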### Recruitment

Contact details of potential study participants for both groups will be obtained from the residents’ registration offices of the chosen study regions of Freiburg and Mannheim, which will enable a random sample of fathers of an infant to be drawn. Due to the random selection of fathers of an infant, a balanced distribution of the children’s age between 0 and 12 months can be expected. Since a request for a sample from the residents’ registration offices takes two days to process, it is guaranteed that all included fathers of an infant will have become a father of a newborn within 12 months prior to this survey. At the same time, the residents’ registration offices of Freiburg and Mannheim will draw the matched control group. The information provided by the residents’ registration offices will include contact details as well as descriptions of the men in the samples according to the variables age, nationality and marital status. After obtaining these sample descriptions, information about the study and a consent form as well as a questionnaire will be sent by post to both groups. The questionnaire is reduced to central variables and a prepaid return envelope will be attached, as these measures are associated with an increased response rate [46].

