#### Prevalence

The prevalence in different time periods after childbirth will be measured as a secondary objective, assessed using the PHQ-9. The age of the child in weeks will be recorded by calculating the time between the date of childbirth and the date on which the questionnaire is completed.

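### The stated power above 80% for month-by-month differences among fathers (ω = 0.1) is not reached by a 12-month comparison of about 1150 fathers, which has about 60%

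*Protocol article*

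**What the plan says.** The Sample size calculation section of the protocol article first sizes the primary comparison, 8.0% in fathers against 5.0% in controls, "with a significance level of 0.05 and a power of 80% in a Chi-square test", and concludes that "data from a total sample size of 2300 participants are necessary". It then sets out recruitment: "4600 fathers of an infant will be randomly selected", an equal number of controls is drawn, and "a dropout rate of about 75% is expected for this study".

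The section closes with a second power claim, for the time course after birth. The obtained sample is said to be large enough to detect "small differences in the prevalence of depressive symptoms among the fathers of an infant (ω = 0.1"). The resolution and the power attached to this claim are given as "for each month after birth with a power > 80% using the Chi-square test". No sample size, number of categories, degrees of freedom or significance level accompanies it.

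Two other places bear on it. Under Recruitment, "a balanced distribution of the children’s age between 0 and 12 months can be expected". Under Secondary objectives, Prevalence, "The age of the child in weeks will be recorded", calculated from the date of birth and the date of completing the questionnaire.

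**The concern.** The claim is about differences among fathers, so only responding fathers count towards its sample size. They are half of the expected 2300 respondents. Monthly resolution also spreads the test over many categories, which costs power at a fixed ω. With half the sample and 11 degrees of freedom, power above 80% at ω = 0.1 looks too high.

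Prevalence by time since birth is the first secondary objective listed in the article, and the Discussion names the ability to examine it as a strength of the large sample. If the power figure is too high, a non-significant monthly comparison would look more informative than it is.

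**Working it through.** **Inputs from the article**
- Fathers contacted: 4600. Expected non-response: about 75%. Responding fathers: 4600 × 0.25 = 1150. All respondents: 9200 × 0.25 = 2300.
- Effect size: ω = 0.1.
- Infant ages spread evenly over 0 to 12 months: 1150 / 12 ≈ 96 fathers per month.

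**Assumptions**
- Significance level 0.05. It is stated for the primary test, and no other level is given.
- Degrees of freedom are not stated. A 12 × 2 table gives (12 − 1)(2 − 1) = 11.
- Mean prevalence of 8.0% in fathers, the planning value. It is used only to translate ω into percentages and for simulation.

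**Formula.** Power = P(χ²(df, λ) > c), where λ = N·ω² is the noncentrality and c is the upper 5% point of the central chi-square with the same df.

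**The plan's figure as a 12-month test among fathers**
- λ = 1150 × 0.1² = 11.5, df = 11, c = 19.68.
- Power = 0.596. The stated > 80% is not reproduced.
- Simulated 12 × 2 tables at 8% mean prevalence: 0.593 with alternating high and low months, 0.545 with one high month.
- At a significance level of 0.10 power would be 0.715.

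**What 80% would need at 11 df**
- The required λ is about 16.80, so N = 16.80 / 0.01 ≈ 1680 responding fathers. As a response rate this is 1680 / 4600 ≈ 36.5%, against about 25% expected.
- With N = 1150, the detectable ω is √(16.80 / 1150) ≈ 0.121.

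**Other readings at ω = 0.1**

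| Reading | N | df | Power |
|---|---|---|---|
| 12 months, fathers | 1150 | 11 | 0.60 |
| Five periods, fathers | 1150 | 4 | 0.78 |
| Four periods, fathers | 1150 | 3 | 0.82 |
| Three periods, fathers | 1150 | 2 | 0.87 |
| One month against the other eleven, unadjusted | 1150 | 1 | 0.92 (about 0.86 simulated) |
| The same, Bonferroni over 12 months | 1150 | 1 | 0.70 |
| Two single months compared | 192 | 1 | 0.28 |
| 12 months, all respondents counted | 2300 | 11 | 0.93 |

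**What ω = 0.1 means for one month against the rest**
- Difference = 0.1 × √(0.08 × 0.92) / √((1/12)(11/12)) = 0.02713 / 0.2764 ≈ 0.098.
- Index month: 0.08 + 0.098 × 11/12 ≈ 17.0%. Other months: 0.08 − 0.098 / 12 ≈ 7.2%.
- The gap of 9.8 points is more than three times the 3-point difference (8.0% against 5.0%) that sized the primary comparison.

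**Precision of one monthly rate**
- About 96 × 0.08 ≈ 7.7 cases.
- 95% half-width = 1.96 × √(0.08 × 0.92 / 96) ≈ 5.4 points.

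**The case against.** The strongest objection is that the article never says which test it means. Its wording can be read as one test per month, that month against the others, with 1 degree of freedom. The nominal power is then 92%, and about 86% by simulation with 96 against 1054 fathers, so the stated figure is met. Nor is it an arithmetic error to call ω = 0.1 small, since that is the conventional label. This stands as far as it goes: the claim does not fail under every possible reading. But this reading needs twelve unadjusted tests, and it meets the figure only for a gap of about 10 percentage points.

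A second objection is that twelve categories are nowhere fixed as the analysis. Elsewhere the article speaks of time periods after birth, and four periods give 82%. That is also true, but the power sentence itself names months.

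Some stronger inferences are tempting, and the documents do not support them.
- A reader might conclude that the trial is underpowered. The monthly statement is an added remark: the 2300 comes from the primary comparison.
- A reader might assume that the authors counted controls by using all 2300 men, which gives 93%. Controls have no month after birth, so that would be wrong, but the article does not show how its figure was obtained.
- A reader might convert the meta-analytic rates in the Background (13% at 3 to 6 months, 8.4% in total) into an expected ω. The 8.4% also covers pregnancy, so it is not a postpartum mean and the remaining months cannot be derived from it.
- A reader might say that a null monthly result will be taken as proof of no variation. The article does not say so. That is a risk and not a planned interpretation.

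**Conclusion.** The power sentence is wrong as written for an overall comparison of the 12 months among fathers: about 60%, not more than 80%. This rests on about 1150 responding fathers, even monthly groups, a significance level of 0.05 and 11 degrees of freedom. The first two follow from the article. The significance level is carried over from the primary test, and the degrees of freedom are inferred from monthly resolution.

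Among fathers, more than 80% is reached only with four periods or fewer, or with an unadjusted one-month-against-rest test for a gap of about 10 points. No reading gives month-level detection of modest differences at the stated power. The importance is moderate, because this is a secondary objective that did not determine the number of men contacted.

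**What to change.** Replace the sentence in one of two ways, giving the sample size, categories, degrees of freedom and significance level in either case:
- state about 60% power at ω = 0.1 for a 12-month comparison among about 1150 fathers (11 df, level 0.05); or
- restate the claim of more than 80% for four 3-month periods (3 df, 82% at ω = 0.1).

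Test time since birth with those four periods, or with child age in weeks as a term with few degrees of freedom in a logistic model. Age in weeks is already recorded, and logistic regression is already among the planned methods. Show monthly rates descriptively with confidence intervals.

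The cost is a change of wording and no new data. Recruitment had ended by March 2019 and analysis was still ongoing in August 2019, so the sample cannot grow, but the statement and the planned test could still be corrected. The price is that monthly resolution becomes descriptive. If the analysis plan already defines the periods, only the power sentence needs to be brought into line with it.

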### Trial status

Enrolment for the trial began in September 2018. Recruitment and data collection continued until March 2019. As of August 2019, data management and data analysis is ongoing.

### Exploratory genetic add-on study

First results indicate the relevance of genetic and epigenetic factors in PPD, which show a complex interaction with psychosocial and environmental aspects [63, 64]. Epigenetic mechanisms include, for example, the methylation of the cytosine-pyrimidine ring in CpG-dinucleotides of DNA, which is associated in most cases with a repression (“silencing”) of the gene transcription [65, 66]. Animal and human studies have shown that epigenetic processes represent flexible and temporally dynamic mechanisms that are significantly influenced by environmental factors [67, 68]. In terms of depression in general, changes in DNA methylation patterns have been detected in classical candidate genes [69], and altered methylation patterns have also been reported in the context of postpartum depression [70, 71]. However, the current knowledge refers primarily to epigenetic markers of postpartum depression in mothers. Therefore, epigenetic factors regarding PPD in fathers will be examined in an exploratory add-on study of this project. The add-on study aims to examine currently unexplained neurobiological mechanisms and genetic and epigenetic factors, respectively, as risk markers for the development of PPD in fathers compared to the development of depressive symptoms in men without recent paternity. Genetic polymorphisms or epigenetic processes such as DNA (hydroxy) methylation patterns will be determined in candidate genes that are selected based on a priori hypotheses. The study design follows the design of the main study described above. Together with the questionnaire of the main study, potential participants will receive information and a consent form to take part in a continuing epigenetic study. For the recruitment, all fathers of an infant and all men in the control group will be asked whether they are willing to give a DNA sample by swabbing the oral mucosa for genetic and epigenetic investigations. Participants who give informed consent will be provided with a home use kit, with which they will make a smear of the oral mucosal cells, from which the DNA for genetic and epigenetic analysis will be extracted. The obtained genetic and epigenetic markers will be related to the parameters collected within the main study. Individuals with severe neurological or somatic diseases, a non-Caucasian origin, or excessive alcohol or drug consumption will be excluded. Regarding the analyses, DNA extraction from oral mucosal cells will be carried out at the Laboratory of Psychiatric Genetics and Epigenetics of the Department of Psychiatry and Psychotherapy of the Medical Centre, University of Freiburg and in laboratories of cooperation partners for special analyses.

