## Methods/design

### Study design

A controlled, cross-sectional epidemiological survey in men with new paternity within one year prior to this survey (group 1: fathers of an infant) and a matched sample of men without a newborn child within one year prior to this survey (group 2: control group) will be conducted via postal questionnaires. The aim is to compare the prevalence of PPD in fathers within the first year after childbirth to the prevalence of depressive symptoms in a matched sample of men without a newborn child. As study regions, we chose two cities in Southwestern Germany with varying populations regarding birthrate, employment status, socioeconomic structure, and nationality of inhabitants: Freiburg and Mannheim, with 228,000 and 320,000 inhabitants, respectively. As social factors may influence the development of PPD in fathers and of depressive symptoms in men without new paternity, the use of two structurally different cities as study regions allows the generalizability of the results to be investigated.

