
## Discussion

Our controlled cross-sectional epidemiological study aims to compare the prevalence of PPD in fathers within the first year after childbirth with the prevalence of depressive symptoms in a matched sample of men without new paternity. Furthermore, our study should reveal differences regarding the prevalence of PPD in fathers in different time periods within one year after childbirth. Additionally, potential male-specific symptoms and risk factors of PPD in fathers will be investigated. A further goal is to assess the current healthcare situation of fathers with PPD in Germany. Our findings will contribute to closing the above-mentioned research gaps and offer possibilities to refine healthcare options for fathers with PPD. Compared to previous studies, our study has several methodological strengths. A central advantage is the direct comparison of the prevalence of PPD in fathers of an infant with the prevalence of depressive symptoms in a matched group of men without recent paternity from the general population. The simultaneous detection of depressive symptoms using the same measurement instrument will minimize the risk of producing an estimation bias of the relative prevalence of PPD and thus increase the external validity of the results. The large sample size compared to previous studies will allow us to perform a variety of subgroup analyses. Furthermore, the large sample size and the recording of the date of childbirth and the date of responding to our questionnaire will allow us to examine prevalence differences for several time periods within one year after childbirth and to analyze specific symptoms of PPD and risk factors. A further advantage of our study lies in the consideration of the healthcare situation of fathers with PPD in Germany – an issue that has not been considered in the research so far. By examining these aspects, low-threshold service access can be revealed, enabling important hints to be derived for the development of adequate care options for fathers with PPD. The identification of risk factors for the development of PPD in fathers will allow an early and specific treatment for these men through the utilization of adequate healthcare offers. Finally, genetic and epigenetic risk patterns of PPD to be identified in the exploratory add-on study might serve as future biomarkers for early interventions or even personalized preventive measures in men at risk of PPD.

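### One methylation sample in a cross-sectional add-on can show association with depressive symptoms, but not risk for developing paternal postpartum depression

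*Protocol article*

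**What the plan says.** The Exploratory genetic add-on study section of the Protocol article sets its aim for genetic and epigenetic factors together: they are to be examined "as risk markers for the development of PPD in fathers compared to the development of depressive symptoms in men without recent paternity". On design it says "The study design follows the design of the main study described above", and the Study design section defines that design as "A controlled, cross-sectional epidemiological survey in men with new paternity within one year prior to this survey".

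The order of contact is also given. "Together with the questionnaire of the main study, potential participants will receive information and a consent form to take part in a continuing epigenetic study". Then: "Participants who give informed consent will be provided with a home use kit". The resulting data are used as follows: "The obtained genetic and epigenetic markers will be related to the parameters collected within the main study". The main-study parameters include the PHQ-9 (Primary objective; Table 1).

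The same section says of the marker itself that "epigenetic processes represent flexible and temporally dynamic mechanisms that are significantly influenced by environmental factors". The Discussion then looks ahead: "genetic and epigenetic risk patterns of PPD to be identified in the exploratory add-on study might serve as future biomarkers for early interventions". It extends this to prevention tailored to men at risk.

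**The concern.** Calling something a risk marker for the development of a condition is a statement about time: the marker is present before the condition and distinguishes those who will get it. A DNA polymorphism meets the temporal part of this whenever it is sampled, because it does not change with mood. Methylation and hydroxymethylation do not meet it by default. On the article's own description they can shift with environment, and a depressive episode, its treatment, or exposures that accompany it are all plausible sources of such a shift.

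The article nevertheless makes one claim for both kinds of marker. If it carries through to the results, a methylation difference that is a consequence of being depressed could be presented as a signal for early identification or prevention. A reader planning a screening or prevention study would then be relying on a temporal order that was never observed.

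**Working it through.** No arithmetic applies. The article states no sample size, effect size or swab interval for the add-on, and the main-study sample size does not bear on this point. The check is to set the statements side by side.

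1. **Number and timing of measurements.** The add-on adopts the main design, which is a cross-sectional postal survey with one questionnaire. One swab per consenting man is described. No sample before symptom onset, no second swab and no follow-up is described.

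2. **Sequence.** (a) Questionnaire, information and add-on consent form are mailed together. (b) The man consents. (c) A kit is provided. (d) He takes the swab. (e) The markers are related to the main-study data. The kit comes only after consent, so the swab probably follows the PHQ-9. That order is an inference, and the interval is not stated.

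3. **Nature of the marker.** The add-on section itself calls epigenetic processes dynamic in time and significantly influenced by environment. It gives no timescale for change.

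4. **What 1 and 3 allow.** Suppose methylation at some candidate gene differs between men above and below a PHQ-9 threshold. Three explanations fit the single sample equally well: the difference was there before the episode; the episode, its treatment or an associated exposure produced it; or the two have no temporal link. Nothing in the described data separates them.

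5. **Whether other items help.** Table 1 lists five items on the presence and duration of the current episode and on previous episodes. These date the symptoms retrospectively. They supply no earlier methylation value, so they cannot establish that the marker came first.

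6. **What 2 adds.** If methylation tracks symptoms at the time of the swab, pairing it with an earlier PHQ-9 may weaken the observed association. The dates that the article names are the child's birth and completion of the questionnaire (Table 1; Secondary objectives, Prevalence). Without the interval and the stability of both measures, the size of the loss cannot be derived.

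7. **Polymorphisms.** Steps 4 and 6 do not apply to them. Their temporal precedence over symptoms is secure, although an association would still be open to confounding and selection like any other result from this survey.

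**The case against.** The strongest reply is that the claim is already modest. The add-on is labelled exploratory throughout, it only aims to examine factors as risk markers, and the biomarker sentence says they might serve. The main study uses the term risk factor just as loosely for cross-sectional questionnaire items. This lowers the seriousness but does not remove the point. The hedge in the Discussion attaches to the later use of the patterns, not to their status as risk patterns. The methylation claim also sits beside the article's own statement that the marker is dynamic. The limitations that the Discussion goes on to name (recruitment, questionnaire burden) do not include temporal order.

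A second reply is that kit contents, swab dates and maximum intervals are operational details that an article leaves to the full protocol. That stands. The article does not say that no swab date is kept, and its silence is not held against the plan here.

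A reader might go further in three ways that the documents do not support:

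- **That the postal delay creates the reverse-causation problem.** It does not. A swab taken on the day of the questionnaire would be just as open to it; the limit comes from the single cross-sectional sample.
- **That the delay disturbs the comparison by month after birth.** That comparison, in Sample size calculation, concerns prevalence of depressive symptoms and does not involve the swab. No analysis of methylation by month is stated.
- **That the loss of association can be quantified.** This would need an assumed lag, an assumed correlation between PHQ-9 scores at the two times, and the further assumption that methylation reflects only symptoms on the day of the swab. If methylation instead follows from the earlier episode, the earlier PHQ-9 could be a reasonable comparator.

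**Conclusion.** The point holds for methylation and hydroxymethylation, and it concerns what may be concluded. As described, the add-on can report that methylation is associated with depressive symptoms. It cannot show that methylation marks risk of developing PPD. This rests only on the stated cross-sectional design, the single sample with none before onset, and the article's own account of epigenetic processes.

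The timing of the swab is a secondary matter. It rests on the inference that the questionnaire is completed before the kit is used, the gap may be short, and its effect has no size that the article allows one to state. The primary objective, the other questionnaire analyses and the temporal reading of the polymorphism results are not affected. The point is modest in weight but worth correcting, since it changes the conclusion that the add-on can draw.

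**What to change.** **Wording.** In the Exploratory genetic add-on study section and in the Discussion, keep the risk-marker and risk-pattern language for genetic polymorphisms only. Describe (hydroxy)methylation as a correlate of current depressive symptoms, and say that the direction of any association cannot be determined. This needs no new data.

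**Analysis.** Where a swab date or kit-receipt date was kept, compute the interval from questionnaire to swab, adjust the methylation models for it, and repeat them in men with a short interval. Adjustment alone does not make the two measurements concurrent; the short-interval analysis is the more informative check. The cut-off should be fixed before the methylation results are seen.

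**Collection.** Trial status says that recruitment and data collection ran until March 2019 and that analysis was under way in August 2019, so a change to the kit helps only kits not yet sent. For any such kits, add a swab-date field and a PHQ-9, and relate methylation to that PHQ-9.

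**Cost.** Two passages reworded, one covariate and one sensitivity analysis; for any remaining kits, a few minutes per participant. The price is a more modest claim for methylation. The interval analysis is possible only if dates were recorded, and neither it nor a PHQ-9 in the kit would establish that methylation preceded the symptoms.
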